#### Phase 2 – Full Collection

The participant population is the same as pre-testing participants.

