## **5.0 Research Locations and Sample Size:**

### **5.1 Research Locations**

During pretesting, participants will be recruited from a variety of retail food establishments in the Boston area, including farmers' markets, grocery stores, and specialty food stores. The research will be conducted at a table located within the establishments' retail space. The first phase will include the Medford Farmer's Market, Stop & Shop and Daily Table.

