#### Phase 2 – Full Collection

During full collection, participants will be recruited from a variety of retail food establishments in the Boston area, including farmers' markets, grocery stores, and specialty food stores. The research will be conducted at a table located within the establishments' retail space. The first phase will include Stop & Shop, Daily Table and the Big Y.

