### Phase 2 – Full Collection

The second phase of this study involves full collection of the experiment using our survey on Qualtrics in the Winter / Spring of 2023. A table will be set up for willing market shoppers to stop and take the survey on iPads provided by Tufts. The survey is expected to take 15-20 minutes to complete.

As part of the choice experiment section, participants will be presented with choices between two to three snack food products and accompanying renderings of food labels for each product. Participants select only one product on each choice scenario (they will be exposed to 8 choice scenarios). Alternatively, if participants don't want to choose any of the snack products, they can opt out by choosing the "no purchase" option. After they finish making their nine choices, they will randomly pick a number to select one of the nine choice scenarios as the binding choice scenario. Participants will only pay for the (one) snack product they chose in the binding choice scenario. If the participant selected the "no purchase" option in the selected binding choice scenario, they won't receive a product and won't have to pay anything. The research team will have the snack products readily available so participants can have their product as soon as they pay for it.

Since the Real Choice Experiment mandates that the selection is binding and that the subject will pay for their chosen product, the research team will give participants \$5 cash at the beginning of the study after they signed the consent form and answer the screening questions. The screening questions are if participants are 18 years or older and if they are responsible for shopping for food for the household.

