**9.0 Recruitment Methods:**

For pre-testing, there will be a table at the establishments where any shopper 18 years and responsible for food shopping for their household will be invited to complete the survey. Participants will be recruited while they patronize the establishments by inviting them to sit with a research team member at the study table. Prospective subjects will be informed of the compensation provided for participation. Please see the attached recruitment scripts and materials.

Phase 2 – Full Collection

The recruitment method is the same as in pretesting.

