#### Phase 2 – Full Collection

Participants will be provided with a total value of up to \$15.00. Up to \$5.00 will be used to purchase study products at the study site from one of the research team members. Participants will keep the change for this \$5.00. If the snack product is less than \$5, participants will be able to keep the change from the purchase. If for the selected binding choice scenario, the participant selected “no purchase”, the participant will be able to keep the \$5. An additional \$10.00 will be given to participants in the form of gift cards / vouchers from Stop & Shop, Daily Table or the Big Y, depending on where testing takes place. Vouchers / gift cards will be handed to the participant by a research team member once the survey has been completed.

Participants will be made aware of the compensation amount before beginning the survey. After completing the survey, they will be provided the chosen study product and remaining monetary compensation. Participants will only receive compensation if they complete the experimental portion of the survey.

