## **17.0 Data Management and Confidentiality:**

The research team members will have access to survey responses, but no members will have access to identifying survey response information, as such information will not be collected. No personally identifiable data will be collected, and no data will be retained for further analysis beyond the improvement of the survey for Phase 2. At the time of administration, survey responses will be collected via Qualtrics on an electronic tablet. After survey completion, responses obtained from participants for each question will be stored within the password-protected Tufts Qualtrics site. Data reports will be exported as CSV. files, and stored within a private, Tufts-affiliated Box drive (a secure, cloud-based file storage platform), available only to research team members. No survey data will be stored on the local device. Data will be available to [name] and other research team members until the team improves the survey instrument, which might take up to 6 months. After this time data will not be retained anymore.

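### Phase 2 does not screen out pretest participants or repeat takers, and their responses could not be separated afterwards; one extra screening question is a cheap improvement

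*Combined protocol and SAP*

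**What the plan says.** **Sites.** Section 5.1 lists the pretest sites as the Medford Farmer's Market, "Stop & Shop and Daily Table". For full collection it says: "The first phase will include Stop & Shop, Daily Table and the Big Y". Two of the three named retailers are common to both phases. Branches are not given.

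**Population and recruitment.** Section 3.0 says of Phase 2: "The participant population is the same as pre-testing participants". Under section 9.0, "any shopper 18 years and responsible for food shopping for their household will be invited to complete the survey", and for Phase 2, "The recruitment method is the same as in pretesting".

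**Screening.** The Phase 2 procedures in section 6.0 give the complete screen: "The screening questions are if participants are 18 years or older and if they are responsible for shopping for food for the household".

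**Payment.** Section 11.0, Phase 2: "Participants will be provided with a total value of up to" $15.00, made up of $5 for the purchase task and a $10 gift card or voucher. No once-only limit is stated.

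**Data.** Section 17.0: "No personally identifiable data will be collected". Phase 2 handling is the same apart from a retention period of up to 2 years. Section 10.0 has each participant sign a paper consent form, but no link from that form to the survey response is described.

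**Analysis.** The Data Exclusion and Missing Data parts of the analysis plan remove people with unanswered choice scenarios, missing trust answers or straightlining. They have no rule for duplicates or earlier exposure.

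**The concern.** A regular customer who took the pretest in summer 2022, or Phase 2 on an earlier trip, passes the screen again and can be paid again. Two things are at stake.

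First, the Inference Criteria plan to compare choices before and after the label is put on the snacks. Someone who has already been through the survey has seen the labels, so their before-label choices are no longer made without that exposure. Pretest participants were also asked for feedback on the survey.

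Second, a repeat taker contributes two sets of choices that the analysis would treat as two independent people, which makes standard errors too small.

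Without a flag at collection, neither effect can be removed or examined in a sensitivity analysis.

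**Working it through.** The plan's own figure is a Phase 2 sample of 350-400, justified by saturation. No power, effect size or variance is given, so it cannot be re-derived, and nothing here depends on it. The gap itself is shown by the text. The arithmetic only bounds its size.

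**Inputs from the protocol:** Phase 1 up to 100 participants; Phase 2 N = 350-400; payment up to $15; Phase 2 survey 15-20 minutes.
**Assumed, not in the documents:** the return rate r, the shift in choice probability among returners, and the number d who take Phase 2 twice.

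**Step 1: pretest participants returning.** Records k = 100 × r; share f = k / N; bias in an overall proportion = f × shift. The shift is set at 20 percentage points for illustration.

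| Assumed return | Records | Share, N = 400 | Share, N = 350 | Bias in points (400 / 350) |
|---|---|---|---|---|
| 5% | 5 | 1.25% | 1.43% | 0.25 / 0.29 |
| 10% | 10 | 2.5% | 2.9% | 0.50 / 0.57 |
| 20% | 20 | 5.0% | 5.7% | 1.00 / 1.14 |
| 100% (ceiling) | 100 | 25.0% | 28.6% | 5.0 / 5.7 |

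For comparison, the standard error of a proportion near 0.5 with one choice per person is √(0.25/400) = 2.5 points or √(0.25/350) = 2.7 points. Across the 5-20% range the bias stays below half of that. Pooling several choices per person would lower the standard error, so this comparison is only a guide.

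**Step 2: repeats within Phase 2.** Suppose N records include d people who each answered twice, with fully correlated answers (the worst case). The variance of the total is (N − 2d)σ² + 4dσ² = (N + 2d)σ². Hence n_eff = N² / (N + 2d), and the true standard error is √((N + 2d)/N) times the reported one.

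- d = 10: 400²/420 = 381 and 350²/370 = 331; true standard error larger by 2.5% and 2.8%.
- d = 20: 400²/440 = 364 and 350²/390 = 314; true standard error larger by 4.9% and 5.6%.

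Unlike pretest returners, who cannot exceed 100, d has no ceiling stated in the plan.

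**Step 3: incentive.** $15 / (20/60 h) = $45 per hour and $15 / (15/60 h) = $60 per hour, taking the maximum payment, offered to people where they already shop.

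**The case against.** The case for leaving the plan alone is that the effect is hypothetical and probably small. Much of that stands, and it rules out several stronger readings.

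- **That earlier takers will enter with carry-over.** A reader might infer this from the shared sites. The documents give no return rate and name retailers without branches. The phases are about half a year apart, and the instrument was edited between them.
- **That a quarter or more of Phase 2 could be pre-exposed.** The 25-29% ceiling needs every pretest participant to return, including those met at the Medford market, which is not a named Phase 2 site. On an equal split over the three pretest sites (assumed), about 67 came from the shared retailers.
- **That repeats cannot be found at all.** Names are signed on paper consent forms, and a team member sits with each participant, so a repeat name could be noticed. What remains true is narrower: no described link would let the matching responses be identified and removed.
- **That returners game the payment rule.** First-time takers are told it too. Section 2.0 describes informing participants of the random binding draw, and section 11.0 has the compensation disclosed beforehand.
- **That the problem sits in the two shared retailers.** Repeats within Phase 2 can equally occur at the Big Y.

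It is also fair to say that no objective requires label-naive participants, and that a shift common to all treatments would largely cancel between treatments. It would not cancel if earlier exposure changed mainly the before-label choices. The attached recruitment script and consent form are not available here and may contain a once-only statement. If so, the protocol should carry it as well.

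**Conclusion.** The point holds as a gap in eligibility and data handling. As written, Phase 2 admits pretest participants and repeat takers, and their responses could not be separated in the de-identified data. It does not show that the results will be materially biased. With an assumed 5-20% return, 5-20 records (1.3-5.7% of Phase 2) would be pre-exposed. Even a 20-point shift in those people would move an overall proportion by about 0.3-1.1 points, against a standard error of about 2.5-2.7. Ten to twenty people taking Phase 2 twice would leave standard errors about 2.5-5.6% too small in the worst case. These sizes rest on the assumed return rate, shift and number of repeats; the gap itself does not. It merits correction because prevention is nearly free and the affected records cannot be recovered afterwards. This is a cheap improvement, not a design flaw that threatens the study.

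**What to change.** In section 6.0, Phase 2 – Full Collection, add a third screening question, asked before the $5 is handed over: *Have you taken this snack survey before, at this or another store?* Do not enrol anyone who answers yes. State in section 9.0 that each person may take the survey once, counting the pretest, and make the recruitment script and consent form agree. Keep the question to the shopper's own participation, since asking about companions would exclude people who never took the survey.

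The cost is one question, one or two protocol lines and a few shoppers turned away. No identifiers or extra staff are needed, and the target of 350-400 is unchanged. The answer is self-reported and the payment gives some reason to deny earlier participation, so the question reduces repeats without eliminating them.

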**6.1 Additional Safeguards for Special Populations:**

NA

**7.0 Investigational Medical Devices:**

NA

**8.0 Incomplete Disclosure or Deception:**

NA

**9.0 Recruitment Methods:**

For pre-testing, there will be a table at the establishments where any shopper 18 years and responsible for food shopping for their household will be invited to complete the survey. Participants will be recruited while they patronize the establishments by inviting them to sit with a research team member at the study table. Prospective subjects will be informed of the compensation provided for participation. Please see the attached recruitment scripts and materials.

Phase 2 – Full Collection

The recruitment method is the same as in pretesting.

**10.0 Consent Process:**

At least one member of the research team will be present during survey pre-testing. Only adults aged 18 years and responsible for food shopping for their household are allowed to participate. The participant will be given the paper Consent Form, which includes details on this study's aims, how the collected anonymized data will be used, and contact information in case of any questions. The participant is asked if they consent to partake in the survey and will sign their name when providing consent. (See the attached Consent form).

Phase 2 – Full Collection

The consent process is the same as in pretesting.

**11.0 Compensation:**

Participants will be provided with a total value of up to \$15.00. Up to \$5.00 will be used to purchase study products at the study site from one of the research team members. Participants will keep the change for this \$5.00. If the snack product is less than \$5, participants will be able to keep the change from the purchase. If for the selected binding choice scenario, the participant selected “no purchase”, the participant will be able to keep the \$5. An additional \$10.00 will be given to participants in the form of gift cards / vouchers from the Medford Farmer’s Market, Stop & Shop, or Daily Table depending on where pretesting takes place. Vouchers / gift cards will be handed to the participant by a research team member once the survey has been completed.

Participants will be made aware of the compensation amount before beginning the survey. After completing the survey, they will be provided the chosen study product and

remaining monetary compensation. Participants will only receive compensation if they complete the experimental portion of the survey.

#### Phase 2 – Full Collection

Participants will be provided with a total value of up to \$15.00. Up to \$5.00 will be used to purchase study products at the study site from one of the research team members. Participants will keep the change for this \$5.00. If the snack product is less than \$5, participants will be able to keep the change from the purchase. If for the selected binding choice scenario, the participant selected “no purchase”, the participant will be able to keep the \$5. An additional \$10.00 will be given to participants in the form of gift cards / vouchers from Stop & Shop, Daily Table or the Big Y, depending on where testing takes place. Vouchers / gift cards will be handed to the participant by a research team member once the survey has been completed.

Participants will be made aware of the compensation amount before beginning the survey. After completing the survey, they will be provided the chosen study product and remaining monetary compensation. Participants will only receive compensation if they complete the experimental portion of the survey.

### **12.0 Economic Burden:**

There is no foreseen economic burden that the participants may bear from participating in this survey. Participants will be given \$5 at the beginning of the study so that they don't have an economic burden. All snack products in the choice experiment study are less than \$5. The funding for purchase of food products come from the grant funding this study. iPads will be provided to the subjects to complete the survey. Individuals cannot take the survey on their own devices.

#### Phase 2 – Full Collection

The compensation is the same as in pretesting.

### **13.0 Recording with Audio, Video, or Photographs**

Audio, video and photographic recording will not be used in this research.

### **14.0 Potential Benefits to Participants:**

There are no direct benefits to individual participants. Subjects are informed that the results from the study will inform policy-makers on views related to food and food labeling, which may ultimately benefit them as consumers, although this would be indirect.

### **15.0 Risks to Participants:**

Participants may be inconvenienced by spending unbudgeted time on their shopping trips. The magnitude of this inconvenience is minor. We do not anticipate any foreseeable risks, discomforts, or hazards related to participants' participation in the research. Data collected from pre-testing will only be used for survey improvement and will not be retained for further analysis.

We further do not anticipate any harm to society or non-participants.

## **16.0 Withdrawal of Participants:**

Participants may withdraw of their own free will at any time. We do not anticipate any reason for researchers to remove participants without their consent; if there are concerns about data quality, this will be addressed during the survey improvement process. If a participant chooses to terminate their participation in the study before completion of the survey, their data will not be collected.

## **17.0 Data Management and Confidentiality:**

The research team members will have access to survey responses, but no members will have access to identifying survey response information, as such information will not be collected. No personally identifiable data will be collected, and no data will be retained for further analysis beyond the improvement of the survey for Phase 2. At the time of administration, survey responses will be collected via Qualtrics on an electronic tablet. After survey completion, responses obtained from participants for each question will be stored within the password-protected Tufts Qualtrics site. Data reports will be exported as CSV. files, and stored within a private, Tufts-affiliated Box drive (a secure, cloud-based file storage platform), available only to research team members. No survey data will be stored on the local device. Data will be available to [name] and other research team members until the team improves the survey instrument, which might take up to 6 months. After this time data will not be retained anymore.

### Phase 2 – Full Collection

The management of data and confidentiality are the same as in pretesting. However, data will be available to [name] and other research team members for up to 2 years. After this time data will not be retained anymore.

## **18.0 Provisions to Protect the Privacy and Confidentiality of Participants and the Research Data:**

Participation in the survey is entirely voluntary. Participants are reminded that they may leave blank any questions they do not wish to answer. Questions do not contain information of a sensitive or personal nature. Participants may skip individual questions, but a complete response will require a response to the choice experiment task questions. Participants will interact with the Tufts team members facilitating the survey's implementation, but no personal information will be provided.

## **19.0 Provisions to Monitor the Data to Ensure the Safety of Subjects:**

No personally-identifying information will be exported from Qualtrics. Data reports will be stored within Box, a private, secure, cloud-based file storage platform. These reports will only be available to the research team.

### Phase 2 – Full Collection

The way to monitor the data to ensure the safety of subjects is the same as in pretesting.

**20.0 Compensation for Research-Related Injury:**

NA

**21.0 Data Sharing and Specimen Banking:**

No personally identifiable data will be collected, and no data will be retained for analysis. Specimens will not be collected.

**22.0 International Research:**

NA

**23.0 Multiple sites:**

NA

**24.0 Reliance Agreements/Single IRB:**

NA

## Analysis Plan

### Statistical Models

We will run the following models to test our hypothesis.

- A binary logistic regression to assess the proportion of participants that choose healthy and unhealthy snack choices. The main predictor variable is the presence of an FDA Healthy, Healthy, or Food Compass Score. Other predictor variables to analyze are generalized trust, personal trust, institutional trust and trust in the government, knowledge, physical activity levels, diet, and sociodemographics.

We will run the same model for each treatment to test, for example, hypothesis H2.

- We plan to run a multinomial logit model (MNL), random parameter model (RPL), random parameter model with EC (RPL-EC), and latent class analysis (LCA) to investigate participants' willingness to pay on each treatment. We will use the presence of a healthy label or food compass score, and price as the main attributes of the utility function for the MNL, RPL, RPL-EC and LCA. However, for the LCA we will use generalized trust, personal trust, and trust in the government (according to hypothesis H2) as consumers' characteristics for the segment membership function.

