### Inference Criteria

We will use the standard  $p < .05$  criteria for the models to determine if the models suggest that the results are significantly different from those expected in the null hypothesis were correct. We will use the Hosmer-Lemeshow test to assess how well the model predicts the dependent variable. In addition, we will use AIC, BIC, log-Likelihood, and  $p^2$  (rho square) to determine the fit of the models. Given the multiple trust indices that we are measuring, we will test for multicollinearity with Variance Inflation Factors (VIF).

We will use statistical tests, such as paired t-tests and ANOVA, to identify the differences between before and after the implementation of the label in the snacks. The same test will be applied to identify differences between treatment results.

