### Data Exclusion

We will verify that each participant answered each of the twelve choice scenarios for the three treatments. Straightlining: If found that participant will be excluded from the survey. Outliers will be included in the analysis.

47  
48 **Missing Data**  
49

50 If a participant doesn't answer any of the twelve choice scenarios, and / or answer the trust-related  
51 questions, that participant will not be included in the analysis.  
52

53 **Exploratory Analysis**  
54

55 If the institutional trust index doesn't predict the probability of choosing a healthy snack labeled with a  
56 Food Compass Score, we will explore the effect of interpersonal trust or generalized trust in the logistic  
57 regression.  
58

59 If the index measuring trust in the government doesn't predict the probability of choosing an FDA-  
60 healthy snack, we will explore the effect of interpersonal trust or institutional trust in the logistic  
61 regression.

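### The logistic model for snack choice has no stated handling of repeated choices by the same person, so p < .05 for trust predictors does not hold its nominal error if the rows are choices

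*Combined protocol and SAP*

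**What the plan says.** Analysis Plan, Statistical Models, opens with "A binary logistic regression to assess the proportion of participants that choose healthy and unhealthy snack choices". It continues: "The main predictor variable is the presence of an FDA Healthy, Healthy, or Food Compass Score". The covariates are mostly characteristics of the person: "Other predictor variables to analyze are generalized trust, personal trust, institutional trust and trust in the government", followed by knowledge, physical activity, diet and sociodemographics. The model is repeated by treatment: "We will run the same model for each treatment to test, for example, hypothesis H2". Inference Criteria sets the threshold: "We will use the standard $p < .05$ criteria for the models".

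The number of choices per person is given in three ways. Section 6.0, Phase 2 – Full Collection, says of participants that "they will be exposed to 8 choice scenarios", and two sentences later says "After they finish making their nine choices, they will randomly pick a number". Data Exclusion says "We will verify that each participant answered each of the twelve choice scenarios for the three treatments". Section 5.2 expects 350 to 400 participants in Phase 2.

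The plan does not define the row of the logistic analysis. It names no method for within-person correlation in that model. Paired t-tests and ANOVA are planned for before/after label differences, and random-parameter and latent-class models for willingness to pay.

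**The concern.** A person who favours healthy snacks in one scenario will tend to do so in the next. An ordinary logistic regression on choice rows ignores this. Trust is a survey measure with one value per person, so its information comes from at most 400 people, while the model would count 400 × 8 = 3,200 rows, or 400 × 12 = 4,800.

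The consequences fall on a stated aim. Objective 2 in section 1.0 is the impact of trust on food choice, and the plan uses this regression to test H2. The result also steers later work: under Exploratory Analysis, other trust indices are examined only if the planned index fails to predict choice. A standard error that is too small can therefore produce a false trust finding and also cancel the planned follow-up.

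**Working it through.** The documents contain no power calculation, effect size or ICC, so there is no figure of the plan's own to reproduce. The check asks what error rate p < .05 would really carry.

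**Inputs**
- Nominal two-sided error 5% (Inference Criteria; two-sided is assumed because sidedness is not stated).
- Choices per person in one fit, m: 8 or 9 (section 6.0, Phase 2), or 12 (Data Exclusion). If the twelve are split evenly over three treatments and the model is run by treatment, m = 12/3 = 4.
- Observed-scale ICC of healthy choice within a person: assumed 0.05 to 0.3.

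**Person-level predictor (trust)**
- Design effect: DEFF = 1 + (m − 1) × ICC.
- True error = 2 × [1 − Φ(1.96/√DEFF)].
- Example, m = 8 and ICC = 0.2: DEFF = 1 + 7 × 0.2 = 2.4; 1.96/√2.4 = 1.265; true error = 20.6%.

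True error (%) at nominal 5%:

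| Choices per fit | ICC 0.05 | ICC 0.10 | ICC 0.20 | ICC 0.30 |
|---|---|---|---|---|
| 4 | 6.8 | 8.6 | 12.1 | 15.5 |
| 8 | 9.2 | 13.3 | 20.6 | 26.6 |
| 9 | 9.8 | 14.4 | 22.4 | 28.8 |
| 12 | 11.5 | 17.6 | 27.3 | 34.5 |

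With one row per person, DEFF = 1 and the error is 5%.

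Simulated pooled logistic regressions (400 people, true null, 1,500 replicates) broadly agree. At ICC 0.10 the error for trust was 10.1% (m = 4), 13.3% (m = 8) and 19.9% (m = 12).

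**Label predictor**
- Label balanced within person, same effect in everyone: naive SE/true SE = 1/√(1 − ICC). This is 1.05 at ICC 0.1 and 1.20 at 0.3, so the true error is 3.9% and 1.9%. The test is conservative.
- Label within person, response differing between people (assumed log-odds slope SD 1.5 to 2.5, intercept SD 1.3): simulated error 8.3 to 16.9% at m = 8 and 11.9 to 22.5% at m = 12. The test is anti-conservative.
- Label fixed within person, m = 8: simulated error 12.9% at ICC 0.10 and 23.7% at about 0.25.

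**After the change**

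With participant-clustered standard errors, simulated error was 4.8 to 5.8% for trust and 4.3 to 7.0% for label across all these scenarios.

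**The case against.** The strongest reply is that the plan never says choices are treated as independent. Its wording refers to a proportion of participants, and with one row per person the problem disappears. It stands that independence is the default of the named model and not a declared rule. However, a person-level binary outcome needs a rule for reducing 8 to 12 choices to a single yes or no, and none is given. Exploratory Analysis also speaks of the probability of choosing a labelled snack, which points to choice rows.

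A second reply is that the size is unknown. This stands. A reader might infer a settled error rate of 12 to 30% or more, but that needs an ICC the documents do not supply and a number of choices per fit on which they disagree. With 4 choices per fit, an error of 30% would require an ICC of about 0.86.

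A reader might also infer that label effects simply get error bars that are too wide. The documents do not support this. They do not say whether label presence varies within a person in each per-treatment fit. The planned random-parameter and latent-class models also allow responses to differ between people, in which case the naive error bars can be too narrow.

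Finally, trust also enters the latent-class membership function, so H2 does not rest on this regression alone. That is fair, but the regression is still judged at p < .05 and still governs the exploratory step.

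**Conclusion.** The concern holds for the person-level predictors, on condition that the rows are choices, which is the natural reading. The direction is then clear for any positive within-person correlation: standard errors for trust are too small. The size is conditional. Over the assumed ICC range, the smallest inflation computed takes 5% to 6.8% (4 choices, ICC 0.05) and the largest to 34.5% (12 choices, ICC 0.3). Neither the ICC nor the number of choices per fit can be fixed from the documents, so these figures are a range and not an estimate.

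For the label predictor, the supportable conclusion is only that its standard error may be wrong, in either direction.

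**What to change.** In Statistical Models, state that the unit of analysis is the choice. Reconcile the 8, nine and twelve choices, and give the number per person and per treatment.

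Fit the logistic model with participant-clustered standard errors, or as a mixed logit with a participant random intercept and a random label slope. A random intercept alone is not an adequate substitute: if people differ in their response to the label, it does not protect the label test.

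For willingness to pay, report the MNL with participant-clustered errors, and state that RPL, RPL-EC and LCA are fitted as panel models in which all of a person's choices share one draw or class.

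The cost is a few sentences and standard software options, with no new data. The downside is that p-values for trust become less favourable.
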